### Data collection and management

2.9

Data will be collected using CRFs throughout both the treatment and follow-up phases of the study. Electronic data will be entered and managed by data administrators at the Beijing eMedyun Software Co., Ltd. (https://edc.emedyun.com/) using management software (e.g., EDC Software). To ensure data integrity and confidentiality, all personally identifiable information will be replaced with study codes. A formal database lock will be implemented by the data management team following study completion. A five-year retention period for all paper records will be maintained post-publication, after which they will be securely destroyed.

### Trial quality control

2.10

Trial quality will be regulated as follows: (a) an independent BL-1 Data and Safety Monitoring Board (DSMB) will be constituted by West China Hospital of Sichuan University to monitor trial conduct and ensure quality throughout the study duration. The BL-1 DSMB will provide independent oversight of the trial’s progress. Its key responsibilities include: ensuring timely documentation and reporting of adverse events; safeguarding participant rights and welfare through verification of informed consent procedures; and critically reviewing all accumulated study data; (b) designated personnel from the Centre for Evidence-based Medicine at West China Hospital, Sichuan University, will provide auxiliary supervision. This includes implementing rigorous quality control measures to verify data accuracy and completeness, facilitating the systematic identification of discrepancies, omissions, or entries requiring clarification or correction.

### Statistical analysis

2.11

Analyses will adhere to the ITT principle, including all randomized patients in their as-randomized groups, provided they received at least one dose of the study intervention (BL-1 or placebo) and completed a minimum of one post-baseline assessment. The PPS and ITT analyses for the primary outcomes will be performed concurrently to verify the consistency of the treatment effects. In cases of discordance between the ITT and PPS, the ITT results will be accorded primacy as the primary analysis for outcome interpretation. The robustness of the trial findings will be substantiated by concordance between the ITT and PPS. The ITT set will be employed for the analysis of baseline characteristics, while the safety set will serve for all safety evaluations. Missing data pertaining to primary outcome measures will be handled through multiple imputation techniques, implemented using R software (version 4.1.2). For remaining categorical variables, no imputation will be performed for missing data, and all available cases will be analyzed as observed.

Continuous variables such as LARSS, EORTC QLQ-C30, and KPS will be subjected to normality hypothesis tests. Continuous variables will be reported as mean (SD) or median (IQR), depending on distributional assumptions assessed through normality tests. Simple and multiple linear regression models will be employed to assess group differences between the BL-1 and placebo groups for both primary and secondary continuous outcomes. Two pre-specified adjusted analyses will be conditionally performed, contingent upon meeting prespecified conditions in the data. The first preadjusted analysis will incorporate *a priori* selected baseline variables, namely age, sex, smoking history, alcohol consumption status, radiotherapy history, and surgical characteristics. The second preadjusted model will further include concomitant treatment as an additional covariate, which is considered a prognostic factor unaffected by treatment assignment. Prespecified subgroup analyses will include the TNM staging of rectal cancer, baseline LARS severity, and three types of surgical resection: low, medium, and high. Categorical variables will be presented as frequencies and corresponding percentages. Primary and secondary categorical outcomes will be analyzed using chi-square tests, supplemented by logistic regression when conditions warrant its application. Adjusted analyses will be extended to categorical outcomes using the same predefined set of covariates as employed in the continuous outcome analyses.

The statistical software employed for data analysis will be IBM SPSS Statistics, Version 29.0. Estimates of intervention effects will be reported as point estimates accompanied by 95% confidence intervals, with a two-tailed *P* value threshold of < 0.05 defining statistical significance.

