#### Trial withdrawal

2.4.4

Patients who require reoperation or chemoradiotherapy due to disease progression, as well as those who withdraw from the study after randomization for any other reason and subsequently cease participation in the intervention or follow−up, will be considered withdrawn from the study. Upon dropout, the investigator is expected to make all reasonable attempts to reach the individual, document the cause of withdrawal, and complete relevant assessments. All data related to the dropout cases should be preserved appropriately for documentation.

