### Sample size

2.8

On the basis of preliminary results from the pilot trial, the BL-1 treatment group had a score reduction of 9.75 ± 2.30 points, whereas the placebo control group had a reduction of 8.55 ± 2.84 points. The overall mean change in the LARSS was assumed to be 9.75 for the BL-1 group and 8.55 for the placebo group. The variances of the two groups were homogeneous, with a standard deviation of 2.5. A superiority design was adopted, with a two-sided test level set at α = 0.05 and a test power of 1-β = 0.9. A sample size calculation was performed based on a balanced design (1:1 allocation), indicating that 93 participants are required per group. Adjusting for an anticipated withdrawal rate below 20% (24), the target enrollment was planned as 117 patients per group, but the intention−to−treat (ITT) and per−protocol set (PPS) analysis sets will be determined based on the final sample size and completion data at trial end. The data collected in this trial will inform future sample size calculations and provide a foundation for the design of subsequent large-scale clinical trials.

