
Prompted by the limited treatment options in current guidelines and documented AEs of available therapies, our team undertook a comprehensive investigation into the pathogenesis of LARS through the lens of TCM, while also systematically reviewing the evidence for TCM and acupuncture efficacy and safety (data unpublished). The current evidence regarding LARS treatments is substantially constrained by methodological quality, necessitating rigorously designed investigations to validate TCM’s therapeutic role. Accordingly, we employed a randomized, double-blind, placebo-controlled design to assess the therapeutic potential and safety of the BL-1 prescription in patients with LARS. The key pathogenic mechanism of LARS is that the disease remains in Yangming, and dampness, phlegm and stasis are intertwined. Therefore, this study aims to assess the therapeutic application of BL-1 in managing LARS across a 4-week intervention period. The clinical effectiveness and safety of BL-1 for the treatment of LARS will be evaluated on the basis of the daily frequency of diarrhea, stool consistency, Wexner anal incontinence score, LARSS, LARS response rate, QOL, KPS score, and reduction in the need for acute treatment.

The following limitations should be considered when interpreting the results of this investigation. First, a notable constraint is the absence of validated objective measures for standardized assessment of LARS outcomes. Inter-individual variability and perceptual differences in symptom reporting may introduce substantial variance in documented drug efficacy profiles. Second, treatment dissatisfaction or intolerability of LARS symptoms may adversely affect patient adherence, thereby increasing the dropout rate. Third, as some participants may reside in other provinces, the quality control of the “direct drug delivery to participants” process requires further refinement. To enhance patients’ comprehensive trial awareness, our study staff received specialized training in establishing effective communication channels and building therapeutic rapport.

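### Agreement between the ITT and per-protocol analyses is made the proof of robustness, but it cannot test whether dropout is informative

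*Protocol article*

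**What the plan says.** All references are to the protocol article.

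- **Section 2.11, Statistical analysis.** The ITT set holds randomized patients as allocated, "provided they received at least one dose of the study intervention (BL-1 or placebo) and completed a minimum of one post-baseline assessment". For missing primary data: "Missing data pertaining to primary outcome measures will be handled through multiple imputation techniques". ITT and PPS are run together on the primary outcome, and ITT takes precedence if they differ. The section then sets the criterion at issue: "The robustness of the trial findings will be substantiated by concordance between the ITT and PPS". It names no other check on the handling of missing data.
- **Section 3, Discussion (limitations).** "treatment dissatisfaction or intolerability of LARS symptoms may adversely affect patient adherence, thereby increasing the dropout rate".
- **Section 2.4.4, Trial withdrawal.** Withdrawals comprise "Patients who require reoperation or chemoradiotherapy due to disease progression, as well as those who withdraw from the study after randomization for any other reason", if they then stop intervention or follow-up. Investigators should try to reach dropouts, "document the cause of withdrawal, and complete relevant assessments".
- **Section 2.8, Sample size.** "The overall mean change in the LARSS was assumed to be 9.75 for the BL-1 group and 8.55 for the placebo group", with SD 2.5, 93 evaluable per group, withdrawal below 20%, and 117 enrolled per group.

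**The concern.** A robustness check is informative only if it could fail when the assumption in doubt fails. Here the doubtful assumption is that patients with no week-4 LARS score would have done as well as the imputation predicts from those who were seen. The PPS, in its usual sense, sets non-completers aside. Multiple imputation, in its standard form, fills their values from completers with similar observed data. If poor responders leave the BL-1 arm more often for reasons the observed data do not capture, both estimates move in favour of BL-1, and their agreement says little about the bias. Patients with no post-baseline assessment are outside the ITT set as well, so neither analysis covers the earliest leavers.

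At stake is the robustness statement in the trial report. Under the rule as written, concordance alone would allow the result to be called robust, although the kind of dropout that the limitations paragraph raises had not been examined.

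**Working it through.** **Inputs.** From section 2.8: difference 9.75 − 8.55 = 1.2; SD 2.5; "with a two-sided test level set at α = 0.05 and a test power of 1-β = 0.9"; 93 evaluable and 117 enrolled per group; withdrawal below 20%.

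**1. The plan's own figure.** n = 2(1.96 + 1.2816)² × 2.5² / 1.2² = 91.2, so 92 per group; the t-based solution is 92.18, so 93. Then 93 / 0.80 = 116.25, so 117 per group and 234 in total. The stated sample size reproduces.

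**2. Smallest significant difference**, 1.96 × 2.5 × √(2/n):
- n = 93 (missing patients add no information): 1.96 × 0.367 = 0.72
- n = 117 (missing patients count in full): 1.96 × 0.327 = 0.64

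**3. Tipping points.** Suppose a fraction f of BL-1 patients is missing and they did δ points worse than imputed, with no shift on placebo. The BL-1 mean falls by f × δ. Significance is lost at δ = (1.2 − critical difference) / f, and the effect is zero at δ = 1.2 / f.

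| Missing | Significance lost (0.72 / 0.64) | Effect zero |
|---|---|---|
| 20% | 2.4 / 2.8 | 6 |
| 15% | 3.2 / 3.7 | 8 |
| 10% | 4.8 / 5.6 | 12 |

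In SD units (÷ 2.5), the 20% row is 0.96 to 1.12 SD for significance and 2.4 SD for zero. The 10% row is 1.9 to 2.2 SD and 4.8 SD.

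**4. Are such shifts conceivable?** A BL-1 dropout who did not improve at all lies 9.75 points below the assumed arm mean. If dropouts in both arms returned to baseline, the difference would be:
- 20% vs 20%: 0.80 × 9.75 − 0.80 × 8.55 = 0.96
- 20% vs 15%: 0.80 × 9.75 − 0.85 × 8.55 = 0.53
- 20% vs 10%: 0.80 × 9.75 − 0.90 × 8.55 = 0.10

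The last two are below both critical differences. This ignores the larger SD that such a mixture would produce.

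**5. Can the two analyses agree while both are biased?** A simulation was run on assumptions that are not in the documents: no true effect, 117 per arm, week-2 to week-4 correlation 0.6, imputation by arm from week 2, completers standing in for the PPS, 1,500 runs.
- *20% dropout, driven by poor week-4 response on BL-1 and random on placebo (two strengths of dependence).* Imputation is biased by +0.28 to +0.38 points and completers by +0.42 to +0.55. The two agree on significance in 83% to 90% of runs. Both are falsely significant for BL-1 in 12% to 20%.
- *Random dropout, 20% in both arms.* Both are falsely significant for BL-1 in 1.6%.
- *Response-driven dropout in both arms, 20% on BL-1 and 10% on placebo.* Both are falsely significant for BL-1 in 5.3%.

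Agreement is therefore common when both analyses are wrong in the same direction.

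**The case against.** The case for leaving the text alone has real substance.

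- *The comparison is there to show consistency, ITT has precedence, and the trial calls itself exploratory.* True, and the precedence rule is sound. But the sentence goes beyond consistency: it says that concordance substantiates the robustness of the findings, without limit.
- *Sensitivity analyses belong in the SAP, which is not shown.* This stands against any claim that none is planned. A reader might infer that the assumption will go untested; the article does not show that. The point here is the stated criterion, which presents concordance as sufficient and needs rewording whatever the SAP adds.
- *The plan does not predict informative dropout.* Correct. The Discussion says only that it may occur. Section 2.11 does not mention missing at random, and the article text does not define the PPS. Both are taken in their usual sense.
- *Dropout related to outcome can still be missing at random.* Also correct. LARSS is recorded at week 2, and dissatisfaction already visible then can be handled if that score is in the imputation model. Access to rescue medication with recorded use (section 2.5.3), telephone follow-up (2.4.1) and attempts to assess dropouts (2.4.4) should reduce the problem. They do not test what remains.
- *Concordance is not empty.* In the simulation the two analyses disagreed on significance in 10% to 17% of the adverse runs, so the comparison has some value, but it is a weak screen.

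**Conclusion.** The point holds as a fault in a stated rule: agreement between two analyses that share most of their observed data does not test informative dropout, so it should not be the ground on which the result is called robust.

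Its size is moderate. A reader might infer that slight departures from the imputation would overturn the trial, and the figures do not support that. At the 20% ceiling, losing significance takes about 1 SD and removing the effect takes 2.4 SD. At 10% missing, removing it takes 12 points, more than the whole assumed BL-1 improvement of 9.75. The missing fraction may well be lower than 20%, because the plan says below 20% and the ITT set already excludes patients without a post-baseline assessment. Dissatisfied placebo patients may also leave, and equal shifts with equal dropout would cancel. Nor do the documents show that the planned estimate will be biased.

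The conclusion rests on the usual meanings of multiple imputation and PPS, on the planned effect and SD, and on a shift in the BL-1 arm alone. The simulation figures depend on its assumed dropout model and only illustrate the mechanism.

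**What to change.** In section 2.11, describe agreement between ITT and PPS as supportive only. Then add that robustness of the week-4 LARSS result to informative dropout is judged by two pre-specified analyses:

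1. A delta-adjusted (tipping-point) multiple imputation, worsening the imputed BL-1 LARSS in 1-point steps until significance is lost, and reporting that shift so that its plausibility can be judged.
2. One imputation in which BL-1 dropouts are imputed from the placebo arm.

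Include the week-2 LARSS in the imputation model, together with the week-6 LARSS and recorded rescue use where available. Keep the precedence of ITT over PPS.

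The cost is a little extra analysis on top of the imputation already planned, and possibly a less favourable robustness statement. The scores and rescue records are already collected, and the sample size stays at 234. Section 2.2 reports 92 patients enrolled and section 2.6 keeps participants and clinicians masked until database lock, so the change can be made before unblinding.

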### Trial setting

2.3

We will recruit 234 LARS patients from the outpatient clinic or inpatient ward of hospitals in Chengdu, China: West China Hospital of Sichuan University, Sichuan Cancer Hospital, and the Affiliated Hospital of Chengdu University of Traditional Chinese Medicine.

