#### Primary outcomes

2.7.1

The primary outcome is defined as the change in LARS score between baseline and week 4. The degree of LARS symptom severity will be measured using the LARS symptom severity score (LARSS) (20). The LARSS is assessed across five key domains: incontinence for flatus, incontinence for liquid stool, stool frequency, clustering of bowel movements, and urgency. The summation of individual item scores yields the total score, which is subsequently categorized according to predefined severity levels. The LARSS will be used to stratify disease severity into three levels: normal (score ≤ 20), mild (21 ≤ score ≤ 29), and severe (30 ≤ score ≤ 42). Treatment response will be evaluated based on changes in severity from original (baseline) level. Patients showing no improvement or any deterioration (e.g., from mild to severe) will be classified as non-responders, while those demonstrating improvement will be categorized as responders (e.g., from severe to mild, from severe to normal, and from mild to normal). The response rate is defined as the ratio of responding participants to the total number of randomized participants, multiplied by 100%.

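### The listed covariates for the LARS change-score analysis leave out the baseline LARS score, adjustment depends on the data, and no model is named as primary: precision is given up, but validity is not

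*Protocol article*

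**What the plan says.** Section 2.7.1 (Primary outcomes) sets the endpoint: "The primary outcome is defined as the change in LARS score between baseline and week 4". Section 2.11 (Statistical analysis) compares the groups on continuous outcomes by simple and multiple linear regression and then describes the adjusted models: "Two pre-specified adjusted analyses will be conditionally performed, contingent upon meeting prespecified conditions in the data". The conditions are not printed.

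The covariates of the first adjusted model are listed: "namely age, sex, smoking history, alcohol consumption status, radiotherapy history, and surgical characteristics". The second model adds concomitant treatment and nothing else. Baseline LARS severity appears in the same section only as a subgroup variable. The score itself is available for everyone, because section 2.4.2 makes a LARS score of at least 20 an entry criterion.

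The only rule of precedence in section 2.11 puts the intention-to-treat set above the per-protocol set. That chooses an analysis set, not a model.

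Section 2.3 names three recruiting hospitals: "West China Hospital of Sichuan University, Sichuan Cancer Hospital, and the Affiliated Hospital of Chengdu University of Traditional Chinese Medicine". Centre is in neither adjusted model, and section 2.6 (Randomization, allocation concealment, and blinding) does not say whether randomization was stratified.

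**The concern.** When the endpoint is a change from baseline, the baseline value of the same score is the natural first covariate. Patients who start high on a bounded scale have more room to fall, and part of any change is regression to the mean. A baseline term removes that part of the variance. The article does not simply leave the covariates to another document: it lists them and omits this one.

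Two features of the text add to the point. Whether an adjusted estimate exists at all depends on the observed data. And with an unadjusted model and two adjusted models in the plan, the text does not say which one carries the conclusion. At stake is the width of the confidence interval around a planned difference of only 1.2 points, and clarity about which estimate is the trial's result.

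**Working it through.** **Inputs from section 2.8 (Sample size).** Mean reductions "assumed to be 9.75 for the BL-1 group and 8.55 for the placebo group", so the difference is 9.75 − 8.55 = 1.20 points. Standard deviation of change: "The variances of the two groups were homogeneous, with a standard deviation of 2.5". Test: "with a two-sided test level set at α = 0.05 and a test power of 1-β = 0.9". Allocation is 1:1.

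**Reproducing the plan's figure.** The normal approximation gives

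n per group = 2 × 2.5² × (1.960 + 1.282)² / 1.2² = 91.2, rounded up to 92.

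The exact two-sample t calculation gives 93 per group, with power 0.9025. Allowing for 20% withdrawal, 93 / 0.8 = 116.25, rounded up to 117. Both stated figures, 93 and 117, are reproduced. The calculation uses the standard deviation of the raw change score, so the trial is sized for the unadjusted comparison.

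**Adding baseline as a covariate.** Let r be the within-group correlation between baseline score and change. The residual standard deviation is then 2.5 × √(1 − r²), and the standard error of the difference at 93 per group is that value × √(2/93). The documents give no r, so a range is assumed. Power and n use the exact t calculation.

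| Assumed absolute r | Residual SD | SE of difference | Power at 93 per group | n per group for 90% power |
|---|---|---|---|---|
| 0 (unadjusted) | 2.50 | 0.367 | 90.3% | 93 |
| 0.1 | 2.49 | 0.365 | 90.5% | 92 |
| 0.2 | 2.45 | 0.359 | 91.4% | 89 |
| 0.3 | 2.39 | 0.350 | 92.7% | 84 |
| 0.4 | 2.29 | 0.336 | 94.4% | 78 |
| 0.5 | 2.17 | 0.318 | 96.4% | 70 |

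The variance falls by the fraction r²: 1% at 0.1, 9% at 0.3 and 25% at 0.5. One degree of freedom for the covariate, out of 184, does not visibly change these figures.

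**Centre.** If centre explained 1% to 5% of the variance (assumed), power by the normal approximation would be 90.8% to 91.9%, against 90.5% without it by the same formula. The gain is small.

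**The case against.** The strongest reply is that nothing in the primary comparison is invalid. With 1:1 randomization, an unadjusted comparison of change scores is unbiased, and the trial has 90% power without any covariate. This stands, and it sets the weight of the point.

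Several stronger readings are tempting, and the documents do not support them:

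- **Chance baseline imbalance as a separate harm.** Such imbalance is already part of the sampling variance of the change score, and so of the standard deviation of 2.5, the confidence interval and the planned power. It is the same loss of precision seen from another side.
- **A large, known gain.** No correlation is given. At 0.1 or 0.2 the gain is about one percentage point of power or less.
- **Inflated type I error.** If the smallest of the three p-values were always reported, simulation gives a two-sided error of about 6.6% to 9.3% when the covariates explain 10% to 45% of the variance (assumed). No sentence in the article permits that choice. Because the sample size matches the unadjusted comparison, a reader may fairly take that model as leading.
- **Undefined conditions.** The article calls them prespecified. The full protocol or analysis plan, not shown here, may define them.
- **Centre as an omitted necessity.** Its contribution is probably small, and the case for it rests mainly on whether randomization was stratified by centre, which the article does not say.

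What remains is that the printed covariate list excludes the baseline score. Even with defined conditions, whether adjustment takes place would depend on the data, and the text names no model as primary.

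**Conclusion.** The point holds as a recommendation to improve precision and to name one model. It is not an error that threatens the trial. The listed covariates omit the baseline value of the outcome, although every patient has one. The unadjusted analysis remains valid with its planned 90% power. Adjusting for baseline would raise power at 93 per group to between 90.5% and 96.4% for an assumed absolute correlation of 0.1 to 0.5, which is equivalent to needing 92 down to 70 per group for 90% power. The size rests wholly on that assumed correlation and on the planning values of 1.2 and 2.5. A reader might infer that the primary result would be biased, underpowered or selected after the fact; the documents show none of these.

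**What to change.** Before unblinding, state in section 2.11 one primary analysis that is always run: linear regression of week-4 LARS score, or equivalently its change, on arm and continuous baseline LARS score. With baseline in the model, the two outcomes give the same treatment estimate. Add centre if randomization was stratified by it. Treat the Wexner, QLQ-C30 and KPS scores likewise, each with its own baseline value. Label the unadjusted model and both listed adjusted models, including the one with concomitant treatment, as supportive, and remove the data-dependent condition from the primary analysis.

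No new data or extra visits are needed, and the baseline term uses one degree of freedom. The cost is administrative. Section 2.12 requires approval by the principal investigators, ethics re-approval and a registry update for an amendment, and section 2.2 reports 92 participants already enrolled. Section 2.6 keeps participants and investigating clinicians masked until database lock, so the change can still be made credibly.

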#### Emergency treatment

2.5.3

Participants who are unable to tolerate their LARS symptoms or are dissatisfied with the treatment effects will, at their request, have the option to receive loperamide Hydrochloride Capsules (Imodium, Xi’an Janssen Pharmaceutical Co., LTD) (17), the guideline-recommended first-line medication for LARS. Detailed recording of medication dosages and treatment duration will be maintained in the case report forms (CRFs).

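### The second adjusted model treats concomitant treatment as unaffected by assignment, which the protocol's own rescue rule contradicts as far as that covariate includes on-trial loperamide

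*Protocol article*

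**What the plan says.** Section 2.11 compares the arms by simple and multiple linear regression and pre-specifies two adjusted analyses, both to be run only if certain conditions are met. The first uses baseline variables (age, sex, smoking, alcohol, radiotherapy history, surgical characteristics). Of the second it says: "The second preadjusted model will further include concomitant treatment as an additional covariate, which is considered a prognostic factor unaffected by treatment assignment". The same covariates carry over to the categorical outcomes.

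Section 2.5.3 describes who may take loperamide during the trial: "Participants who are unable to tolerate their LARS symptoms or are dissatisfied with the treatment effects will, at their request". Dose and duration are recorded in the case report form. Section 2.5.4, whose heading concerns prohibited concomitant medications and treatments, bars other anti-diarrhoeals, other TCM therapies and other LARS interventions during the trial, apart from what the protocol permits.

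The Discussion lists the measures by which the effectiveness and safety of BL-1 will be judged, and ends that list with "and reduction in the need for acute treatment".

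**The concern.** A covariate can be added safely to a randomised comparison if it is fixed before randomisation or truly cannot respond to treatment. Loperamide taken during the four weeks meets neither condition. It is requested because symptoms are bad or the assigned treatment disappoints, so it depends on how the participant is doing and, if BL-1 works, on arm. The Discussion expects exactly that dependence.

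Holding rescue use constant compares BL-1 and placebo patients who did equally badly or equally well in terms of needing rescue. Part of any BL-1 benefit is thereby adjusted away, and the two arms within a rescue stratum are no longer comparable by randomisation. At stake is a pre-specified adjusted estimate of the primary outcome, and of response rates. It could disagree with the main result for reasons unrelated to efficacy, and the protocol's wording would lead readers to take it as a valid adjusted treatment effect.

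**Working it through.** **Step 1: the passages side by side.** Section 2.11 says the covariate does not depend on arm. Section 2.5.3 makes loperamide depend on symptoms and on satisfaction with the treatment effect, both arising after randomisation. Section 2.5.4 leaves loperamide as the only on-trial LARS drug that the article names as available. The Discussion treats less acute treatment as a benefit of BL-1. A variable cannot be both an expected effect of BL-1 and unaffected by assignment.

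**Step 2: the planning figures (section 2.8).** "The overall mean change in the LARSS was assumed to be 9.75 for the BL-1 group and 8.55 for the placebo group", a difference of 9.75 − 8.55 = 1.20. "The variances of the two groups were homogeneous, with a standard deviation of 2.5". The design is planned "with a two-sided test level set at α = 0.05 and a test power of 1-β = 0.9".

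- Normal approximation: n = 2 × (1.960 + 1.282)² × 2.5² / 1.20² = 91.2, so 92 per arm.
- Two-sample t-test: 93 per arm (power 0.903), which reproduces the stated 93.
- Withdrawal: 93 / 0.8 = 116.25, so 117, as stated.

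The sample size is reproduced. It does not decide this point, but it supplies the effect and SD used below.

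**Step 3: how the two estimates are linked.** With a rescue indicator R in a linear model,

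unadjusted = adjusted + γ × (rescue rate on BL-1 − rescue rate on placebo),

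where γ is the coefficient of R. The two agree only if γ is zero or rescue rates are equal.

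**Step 4: illustration, threshold rescue.** The protocol gives no rescue rate, no loperamide effect and no correlation between symptoms at the rescue decision and at week 4; all three are assumed. A patient takes rescue when latent improvement falls below a cut-off; 2,000,000 patients per scenario; true difference 1.20, SD 2.5, loperamide effect zero. Power is approximated at 93 per arm.

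| Rescue, placebo / BL-1 | Adjusted, correlation 0.5 (power) | Adjusted, correlation 0.8 (power) |
|---|---|---|
| 10% / 4% | 1.05 (0.84) | 0.95 (0.81) |
| 20% / 9% | 0.95 (0.78) | 0.81 (0.72) |
| 30% / 16% | 0.89 (0.73) | 0.71 (0.64) |
| 40% / 23% | 0.85 (0.70) | 0.64 (0.58) |

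Without rescue in the model the estimate is about 1.20 and power about 0.90 in every row. Check of Step 3 in the 30% row at correlation 0.8, where γ = −3.438: 1.196 − (−3.438) × (0.158 − 0.300) = 0.708, against 0.709 from the regression.

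With a 2-point loperamide effect, the model without rescue gives 1.08 down to 0.86 (the treatment-policy effect) and the rescue-adjusted model 1.05 down to 0.64.

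**Step 5: illustration, gradual rescue.** Here logit P(rescue) = a − b × (improvement − 9), with improvement the week-4 value before any rescue effect.

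| Rescue, placebo / BL-1 | b | Loperamide effect | Unadjusted | Adjusted |
|---|---|---|---|---|
| 34% / 23% | 0.6 | 0 | 1.20 | 0.91 |
| 34% / 23% | 0.6 | 2 points | 0.99 | 0.91 |
| 34% / 23% | 0.6 | 4 points | 0.77 | 0.91 |
| 12% / 7% | 0.6 | 0 | 1.20 | 1.05 |
| 6% / 3% | 0.6 | 0 | 1.20 | 1.12 |
| 28% / 22% | 0.3 | 0 | 1.20 | 1.10 |
| 24% / 22% | 0.1 | 0 | 1.20 | 1.19 |

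With no loperamide effect, the shortfall over both set-ups runs from 1 − 1.19/1.20 = 1% to 1 − 0.64/1.20 = 47%. In the 4-point row the order reverses: adjusted 0.91 exceeds unadjusted 0.77, and neither equals 1.20.

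**Step 6: no true effect.** In the threshold set-up with a true difference of zero, both models return zero and hold the 5% level, because rescue there depends on arm only through improvement.

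**The case against.** The strongest reply is that section 2.11 does not define concomitant treatment, and the protocol files loperamide under emergency treatment. If the covariate meant only medication in use at entry, or background non-LARS drugs, the problem would largely disappear. That reading is possible but poorly supported: the baseline variables already sit in the first model, the second adds this covariate as a further step, and section 2.5.4 uses the term for treatment during the trial, with an exception for permitted treatments that can cover loperamide. What stands is that the point is conditional on the covariate including on-trial rescue.

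The Discussion's mention of acute treatment is also secondary support. It is not among the outcomes in section 2.7 and is not defined as loperamide. Section 2.5.3 carries the argument.

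A reader might infer more than the protocol supports:

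- *That the main comparison is biased.* It is not. The simple regression and the first adjusted model do not contain this covariate, and nothing makes the second model decisive.
- *That the estimate shrinks by a known amount, or always shrinks.* Rescue rates and the loperamide effect are undocumented, and the adjusted value can lie above the unadjusted one.
- *That the unadjusted estimate is wrong when loperamide works.* It then estimates a treatment-policy effect, which is a legitimate target.
- *That rescue users who improve by a severity band are wrongly counted as responders.* That is a separate question about handling rescue, which an article may leave to the analysis plan.

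**Conclusion.** The point holds in limited form. Calling concomitant treatment unaffected by assignment contradicts section 2.5.3 as far as it includes on-trial loperamide, and the Discussion points the same way. The resulting coefficient answers no clear causal question: it is neither the treatment-policy effect nor the effect without rescue.

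The size is illustrative only. Under the assumed rescue behaviour, with a true 1.20-point difference and no loperamide effect, model 2 returns about 0.64 to 1.19. In the threshold scenarios power at 93 per arm falls from about 0.90 to between 0.84 and 0.58. No false-positive risk appeared in the null scenarios examined.

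The fault sits in a conditional, supplementary model, so it should be fixed; it does not undermine the primary comparison.

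**What to change.** In section 2.11, remove on-trial concomitant or rescue treatment from the second adjusted model, or define the covariate as treatments in use at randomisation. Delete the statement that it is unaffected by assignment for any on-trial treatment. Apply the same change to the categorical outcomes, which inherit the covariate set. Summarise loperamide use by arm (any use, dose, duration) descriptively.

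The cost is a wording change and one table. No new data are needed, because section 2.5.3 already has dose and duration recorded. Section 2.2 reports 92 of the planned 234 participants enrolled, and section 2.6 keeps participants and clinicians masked until database lock and the analysis blinded. The change can therefore be made now without appearing to be driven by results.
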